### Baseline procedures and data collection at the initial visit conducted within 1 month prior to the intervention: (Figure 2)

**Fig. 2 Fig2:**
[figure not shown]
ARTiCO study flow chart. The diagram shows baseline and follow-up procedures in ARTiCO study. SAVR: surgical aortic valve replacement; TAVI: transcatheter aortic valve implantation, NRL: neurological evaluation; NRP: neuropsychological evaluation; MRI: magnetic resonance imaging, QoL: quality of life tests.

Signing of informed written consentClinical data will be collected in a questionnaire specifically designed for this study:o Sociodemographic variables: age, sex, education (years and level of education), hand dominanceo Anthropometric variables: height, weight.o Vascular risk factors: smoking habit (never, current, former), alcohol intake, physical activity level (sedentary, home-activity, outdoor activity and grade), history of hypertension, diabetes mellitus, dyslipidemia, and arrhythmia (atrial fibrillation or another type).o Current drug intake (platelet inhibitors, anticoagulants, lipid-lowering drugs, antihypertensives, hypoglycemic agents, antiarrhythmics, antidepressants).o Vascular events presented prior to inclusion in the study: angina, myocardial infarction, intermittent claudication, transient ischemic attack, and stroke.o Heart Failure: Using the New York Heart Association classification (From class I to IV)o Renal function before treatment (creatinine level and glomerular filtrate)o Total score in EuroScore II  [32]3Neurological evaluationA complete neurological evaluation will be carried out by a neurologist specialized in cerebrovascular diseases. It will include; a complete anamnesis and review of the subject’s clinical history, including data from neuroimaging studies to confirm the existence of previous cerebrovascular pathology in any of its manifestations (Type 1: overt Central Nervous System (CNS) injury; Type 2: covert CNS injury, and Type 3: neurologic dysfunction without CNS injury) following the Neurologic Academic Research Consortium  (NeuroARC) recommendations [33]. Likewise, a neurological examination will be carried out using the National Institutes of Health Stroke Scale (NIHSS) [34] to detect neurological deficit attributable to cerebrovascular lesions, with a score range of 0 to 42, with 0 indicating absence of focal neurological damage. Functional dependence will be assessed with the modified Rankin scale (mRS) ranging from 0 to 6, where 0 indicates functional independence and 6 death [35]. In addition, depressive symptoms will be assessed with the Geriatric Depression Scale (GDS), with scores higher than five indicating probable depression [36], and cognition will be assessed by the Informant Questionnaire On Cognitive Decline in the Elderly (IQCODE) test with scores higher than 57 indicative of probable cognitive decline [37]. The same stroke neurologist will assess all cerebrovascular events that subjects may experience during follow-up.4Neuropsychological assessment:Acquisition, analysis of neuropsychological variables:
Neuropsychological Tests:The same clinical neuropsychologist will conduct the NPS evaluation at the three evaluation times, and the neuropsychologist will be blind to the patient’s treatment group.The neuropsychological battery will last approximately one and a half hours, and it will consist of tests sensitive to vascular cognitive impairment (VCI). Neuropsychological tasks will be categorized into four cognitive domains:
Attention and Psychomotor speed will be measured by the Digit Span forward subtest of the Wechsler Adult Intelligence Scale (WAIS-III) [38], the Symbol Digit Modality Test (SDMT) [39], the Symbol Search subtest of the WAIS-III [38], the Grooved Pegboard dominant hand [40] and the Trail Making Test part-A (TMTA) [39, 41].Verbal and visual memory will be evaluated with the Rey Auditory Verbal Learning Test (RAVLT) 15-word verbal learning test (RAVLT) [42] and the delayed memory recall of Rey's Complex Figure (RCF) [43].Executive functions will be measured by the Digit Span backward subtest WAIS-III [38], the Trail Making Test part-B (TMTB) [39, 41], and the Phonemic Verbal Fluency test (letter M) [44].Visuoconstructive and Visuospatial functions included the copy of Rey’s Complex Figure (RCF) [43] and Block design subtest of the WAIS-III [38].

Also general cognitive functioning will be evaluated before the neuropsychological battery using the MMSE and MoCA tests [31, 45].

The order in the administration of tests will be constant to avoid variability between subjects due to fatigue.

To control for type I errors associated with multiple comparisons and to summarize scores obtained from the wide range of tests used, we will compute a Global Cognitive impairment Index (GCII) as the primary outcome. To this end, all measures will be first transformed to standardized z scores using age and education level corrected norms. The GCII will be computed by averaging all z scores from the different measures and also separately for each cognitive dimension. The final GCII will be a z score with a mean of 0 and an SD of 1 with lower or negative scores reflecting a poorer performance.

In addition, all patients will be classified into one of three groups according to their performance on the neuropsychological battery: a group with no cognitive impairment, a group with mild cognitive impairment (MCI) and a group with moderate cognitive impairment.

MCI will be defined when the results of one or more cognitive domains are 1.5 SD below the mean. Moderate cognitive impairment will be considered when the results of one or more cognitive domains are 2 SD below the mean [46].

5Advanced Neuroimaging study protocol:

Data acquisition

Assessments will be carried out at the CMCiB with an MRI (Cannon MRT-3020 Vantage Galan 3T) dedicated to biomedical research. We will use a 32-channel phased-array head coil with foam padding and headphones to restrict head motion and suppress scanner noise. The MRI protocol will include a set of magnetization-prepared rapid gradient echo (MP-RAGE) T1-weighted images (repetition time [TR]: 8.4 ms; echo time [TE]: 2.7 ms; field of view: 256 mm; flip angle: 9º; and voxel size: 1×1×1 mm3). T2*- weighted images will be acquired using a multi-echo sequence with the following acquisition parameters: repetition time [TR]: 845.8 ms; with the following echo times [TE]: 6.800, 13.600, 20.400, and 27.200 ms; field of view: 245 mm; flip angle: 20º, and voxel size: 0.80×0.80×3 mm3. Fluid Attenuated Inversion Recovery (FLAIR) image will acquire with the following acquisition parameters: repetition time [TR]: 7000 ms; echo time [TE]: 445.5 ms; inversion time [TI]: 2200 ms; field of view: 256 mm; flip angle: 90º; and voxel size: 1×1×1 mm3. DWI will acquire in 48 non-collinear diffusion directions, with a b-value of 1.000 s/mm2, with the following echo planar acquisition protocol: [TR]: 12447 ms; [TE]: 81 ms; field of view: 240×256 mm; flip angle: 90º; and voxel size: 2×2×2 mm3; phase-encoding direction: PA. Two images with a value of 0 s/mm2 and opposite phase-encoding directions (AP and PA) will also be acquired. Intravoxel Incoherent Motion images (IVIM-DWI) will also be acquired with a single-shot spin-echo echo-planar imaging sequence using the following acquisition protocol: [TR]: 6680 ms; [TE]: 90 ms; field of view: 240 mm; flip angle: 90º; and voxel size: 1.5×1.5×5 mm3 with six b-values (50 sec/mm^2^, 100 sec/mm^2^, 300 sec/mm^2^, 600 sec/mm^2^, 1200 sec/mm^2^, and 2400 sec/mm^2^ with three orthogonal acquisition directions for each b-value. Resting-state blood oxygen level-dependent data will be acquired using an echo-planar imaging sequence (repetition time = 2.25 s; echo time = 25 ms; flip angle = 90°; in-plane spatial resolution = 3 × 3 mm2; field of view = 240 × 240 mm2; slice thickness = 3 mm; number of slices = 37; number of volumes = 256; acquisition time = 8:32 min). Participants will be instructed to lie still with their eyes closed but remain awake.

Data analysis

Cortical thickness and volume analysis will be carried out with Freesurfer 7.3.1 (http://www.surfer.nmr.mgh.harvard.edu/), and the pre-processing and analysis of the DWI and resting-state fMRI images FSL 6.0.5.2 (FMRIB's Software Library, http://www.fmrib.ox.ac.uk/fsl/).

DWI pre-processing included motion and eddy current correction using FSL’s Topup and Eddy Correct Tool using the FMRIB Diffusion Toolbox (FDT) (Analysis Group, FMRIB, Oxford, UK) [47]. In order to eliminate spurious voxels, skull stripping of the T2 weighted b = 0 volume was achieved using FSL’s Brain Extraction Tool (BET) and will be used as a brain-mask for all other diffusion maps. FDT will be used for the tensor modeling of the diffusion parameters to produce DTI data. Microstructural maps of axial (AD), radial (RD), and mean (MD) diffusivity and fractional anisotropy (FA) will be entered into group analysis using Tract Based Spatial Statistics - TBSS [48]. All subjects' FA data will be aligned into a common space using the nonlinear registration tool FNIRT [49, 50], which uses a b-spline representation of the registration warp field [51, 52], resulting in all images transformed into 1 mm isotropic, MNI152 standard space. Next, all participants’ FA volumes will average, and a mean FA skeleton will be created from all voxels with an FA threshold = 0.2 to reduce the inclusion of voxels that are likely composed of multiple tissue types or fiber orientations. Each participant's aligned, standard space FA maps will be then projected onto this skeleton to create a 4D skeletonized volume (3D skeletal volume × number of subjects) which will then fed into voxel-wise group statistics. Other diffusion-derived data (AD, RD, and MD) projections on the TBSS skeleton will also be calculated for each subject. The spatial normalization transformations computed for the FA maps will be applied to these maps to achieve their nonlinear registration, which will be projected on the TBSS skeleton. The resulting 4D volumes will also be used for voxel-wise cross-subject statistics. For the analysis of structural connectivity, the probabilistic tractography analysis (Probtrackx2) will be used.

The acquired IVIM-DWI images will be processed using DIPY 1.6.0.[53] IVIM-D and IVIM-f maps will be calculated in native space using the “2-stage Trust-Region Reflective based NLLS fitting method” (TRR) fitting method [54]. The analysis of the resting-state fMRI data will be conducted using probabilistic Independent Component Analysis as implemented in FSL’s MELODIC tool. Data preprocessing will consist of the removal of the first 5 volumes to ensure saturation and adaptation of the subjects to the environment leaving 251 volumes for further analysis, removal of non-brain structures using Brain Extraction Tool, motion correction using MCFLIRT, high-pass filtering with a frequency cut-off at 100 s, spatial smoothing using a Gaussian kernel of full-width half-maximum of 5 mm, intensity normalization, and non-linear registration to the MNI152 standard template. We will discard components representing known artifacts, such as motion, high-frequency noise, or venous pulsation [55, 56] components not located mainly in gray matter, and components not resulting in compact clusters [57] using ICA-AROMA [49]. (Figures 3, 4 and 5)

**Fig. 3 Fig3:**
[figure not shown]
Demonstrates the FreeSurfer pipeline, including tissue segmentation **A**, parcellation based on the Desikan-Killiany Atlas **B**, and estimation of the cortical thickness (**C**) of the structural, T1-weighted acquisition.

**Fig. 4 Fig4:**
[figure not shown]
Processing the diffusion-weighted data. **A** and **B** demonstrates the pipeline for processing the diffusion-weighted data, including estimating the primary direction of diffusion (**A**), and co-occurring fibers at the crossing three major tracts (**B**), using FSL’s DTIFIT and BedpostX. **C**, **D** and **E** shows the parameter estimates **D** (**C**), **D*** (**D**), and f (**E**) of the voxel-wise estimation of Intravoxel Incoherent Motion, while F shows the fitting of the model on a typical voxel.

**Fig. 5 Fig5:**
[figure not shown]
Demonstrates the ICA-AROMA pipeline for cleaning the resting-state fMRI data, including the component assessment (**A**) and a component clearly showing motion artefacts (**B**).

### Procedures and data collection during the intervention and hospitalization period

Intraoperative features:Extracorporeal circulation time, coronary ischemia time, and orotracheal intubationBleeding from drainsTransfusion of blood productsTypes of prosthesis and approach: in SAVR (Percebal S (LlivaNova PCL) which is a suture-less bio-prosthesis, and in TAVI (Sapien 3 (Edwards Lifesciences).Total of intubation hours and need for tracheostomy

During hospital admission

Definite morbidity at discharge:

Stay in the ICU for>48 hours, in the ward for more than 10 daysRespiratory, renal (RIFLE criteria), infectious, cardiac rhythm complications (endo-cavitary pacemaker implant)Neurological complications: stroke, transient ischemic attack, episodes of disorientation and seizuresDegree of dependencyReadmissions (in the critical/semi-critical unit)Valvular hemodynamics (echocardiographic data)

Definite Mortality at discharge:

Immediate: <72 hours post-procedureHospital: during hospitalization and/or first 30 days post-procedure

Follow-up clinical variables: All complications and mortality at 6 months and one year will be collected, as well as valve hemodynamics and functional class in both groups.

### Early visit procedures of the study protocol, planned to be performed approximately one month after the operation:

Neurological EvaluationThe stroke neurologist will question the patient to rule out the existence of cerebral vascular events from the baseline visit and, if detected, will carry out an etiological study thereof. The events will be classified following the (NeuroARC) recommendations. Regardless of the existence of cerebral vascular events, the neurologist will perform the neurological examination with the NIHSS and will administer themRS, as well as the GDS and the SS-IQCODE.

2Neuropsychological assessment:The same neuropsychologist who administer the tests at the baseline visit will administer them again at the monthly visit. I would like to draw attention to the fact that the tests will be reviewed by another neuropsychologist of the study to avoid errors before transferring these results to the electronic data notebook. This procedure will be performed at all the study visits in which the neuropsychological study will be administered.

3Advanced Neuroimaging study protocol:The same study protocol will be administered at this visit. Two blinded investigators to the study group assignment will read the images.

### Late visit procedures of the study protocol, planned to be performed approximately one year after the operation:

Neurological EvaluationIn the final visit of the study, the vascular neurologist will ensure through questioning and review of the medical history that the patient has not suffered any cerebral vascular event, and if so, it will carry out an etiological study of the same. The events will be classified following the NeuroARC recommendations. Regardless of the existence of cerebral vascular events, the neurologist will perform the neurological examination with the NIHSS and will administer themRS , as well as the GDS and the SS-IQCODE.

2Neuropsychological assessment:The same neuropsychologist who administered the tests at the baseline and early visit will administer them again at the year visit.

3Advanced Neuroimaging study protocol:The same study protocol performed at the baseline, and early visits will be administered at this visit. As in previous visits, two investigators blinded to the study group assignment will read the images.

### ARTiCO clinical and image database

Clinical data will be recorded in case report forms (CRF). The data from the neuropsychological and neuroimaging studies will be collected in different CRFs that the one that stores the clinical data to maintain blindness. The images obtained in advanced MRI studies will be stored on specific CDs to be analyzed afterward. A prospective electronic database with clinical, neurological, neuropsychological, and neuroimaging variables will be created, including all study visits.

### Statistical considerations

The sample size calculation will be based on the main variable of the study, Impairment Index or Global Cognitive Impairment Index, which will be handled as a standardized normal distribution (mean=0 and SD=1). The way to transform the values of every subject to a standardized value is using the formula (value-mean)/SD. With this approach, we can estimate the difference between groups as a difference in the standardized normal distribution (z score), avoiding to approximate or guess values of SD that we do not previously know.

Establishing an alpha error of 5% and a beta error of 20% (80% statistical power), for a two-sided analysis and an effect size to observe defined as a minimal difference in z score of 0.67. Applying these criteria, an estimate of 36 patients per group is obtained. Assuming a loss of follow-up of 10%, we aimed to recruit 40 patients per group. The statistical package used for sample calculations was Stata 14.2 (StataCorp LLC, College Station, Texas, USA).

A descriptive analysis of the sample will be carried out based on the characteristics of each variable. Continuous variables will be expressed as mean and 95% confidence interval, or median and interquartile range for each of the study groups, choosing the most appropriate description according to the result of the Shapiro-Wilk normality test. Categorical variables will be expressed with their absolute frequency (count) and relative frequency (as a percentage).Data cleansing and exploration of missing values will be carried out. Missing data greater than 10% will be considered excessive, deciding whether to maintain the variable in the study according to its importance in the literature and in the study design. For missing data recognized as excessive in clinically important variables, the dataset will be completed using multiple imputation techniques. Student t-test will be preferred for the crude comparative analysis between groups as a bilateral parametric test that will allow us to find differences in both directions of the hypothesis, given the heterogeneity of the existing literature. Equality of variances will be tested using the Levene test to adjust the standard error in the comparison. Sample size should ensure the conditions of application of parametric tests.The statistical adjustment of confounding factors and interaction of predictors will be carried outby building an explanatory model using multivariate linear regression, thus obtaining the coefficient corresponding to the main variable adjusted by the rest of potentially confounding or effect-modifying variables. First, a univariate screening of variables will be carried out, introducing in the model those which present confounding criteria based on the Pearson correlation test. Subsequently, first-order interactions will be explored based on statistical significance tests. The adjustment of confounding factors will be carried out based on relevant modification criteria (larger than 10%) of the model coefficients, according to the methodology described by Kleinbaum et al [58], and applying the principle of parsimony. The search for independent predictors of neuropsychological dysfunction will be carried out using a predictive approach of hierarchical logistic regression with a stepwise backward methodology.An analysis of residuals and extreme values will be carried out to verify the robustness of the built model. For the rest of the secondary hypotheses, mean comparison techniques (Student's t-test with adapted standard error) and proportions (chi-square) will be used.

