Along with the neuropsychological study, which is the goal standard in the diagnosis of cognitive impairment, including VCI, neuroimaging with MRI is key to objectifying the lesions that are probably the origin of alterations in cognitive domains. In addition, functional MRI will allow us to study pathways and brain functions, as well as establish the correlation between the findings with the results of the neuropsychological study. The potential usefulness that can be obtained with the data from our study could mean using neuroimaging as an alternative to the neuropsychological study in those patients with cognitive alterations or with language alterations, such as aphasia, or of the senses such as hearing or sight, that do not allow the administration of all or some neuropsychological tests.

Strengths of this study are: 1). Although patients will not be randomized between SAVR and TAVI, they are eligible for inclusion in the study only if they are suitable for both techniques; therefore the groups will be comparable; 2). To the best of our knowledge, this is the first study that simultaneously uses an extensive neuropsychological study, with a battery designed to evaluate all domains likely to be affected in the VCI, and an advanced MRI study, with sequences to assess structural damage as well as a functional MRI to compare SAVR and TAVI in patients with severe aortic stenosis; 3). In addition, these studies will be carried out pre-treatment, in the early phase and in the late phase; 4). and will have the participation of a vascular neurologist who will evaluate the patients and the clinical events that they may present following the recommendations of the NeuroARC.

We hope that all the information obtained from ARTiCO study will contribute to a better understanding of the changes that occur in neurocognition after the two distinct types of treatment available for severe AS and therefore, that it helps Heart Teams in decision-making.

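### Imputation is triggered only above 10% missing, so at the planned 10% loss the primary cognitive comparison is by default a complete-case analysis, whatever the reason for or balance of the losses

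*Protocol article*

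**What the plan says.** The rule stands in the protocol article under Statistical considerations. It first sets a threshold: "Missing data greater than 10% will be considered excessive, deciding whether to maintain the variable in the study", with the decision resting on the variable's importance in the literature and in the design. It then limits imputation to that case: "For missing data recognized as excessive in clinically important variables, the dataset will be completed using multiple imputation techniques". No method is given for 10% or less. The analyses named in the same section are a Student t-test for the crude comparison and linear regression for the adjusted one.

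The sample size paragraph of that section arrives at 36 per group and adds: "Assuming a loss of follow-up of 10%, we aimed to recruit 40 patients per group". The Methods/design part of the abstract repeats 40 per group to end with 36.

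Three other places bear on who would be missing:

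- The early and late visit sections keep the neurological examination for everyone, with or without a cerebrovascular event, and repeat the neuropsychological battery without any exclusion for stroke.
- The Discussion recognises that there are patients with cognitive, language or sensory problems "that do not allow the administration of all or some neuropsychological tests".
- The section on procedures during the intervention and hospitalization has mortality collected to one year, but the article does not connect death to the GCII analysis.

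**The concern.** Whether a completers-only comparison is biased depends on why scores are missing and on whether the reasons and amounts differ between procedures. A percentage threshold measures neither. The threshold is also set at the very loss that the study expects, so if things go as planned the safeguard stays off.

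This study compares two procedures on cognitive harm. Death and severe neurological injury are possible consequences of both, and both can remove a patient's score. If one procedure causes more of them, it loses more of its worst scores and looks better on the primary outcome than it should. The article states this rule outright, so the point concerns a choice already made and not detail left to an analysis plan that is not shown.

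**Working it through.** **Inputs from the document** (Statistical considerations): alpha 5% two-sided, power 80%, difference 0.67 z, SD 1, 36 evaluable and 40 recruited per group, 10% loss, imputation only above 10%.

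**Input not in the document:** D, the gap in mean GCII between observed and missing patients. It is assumed to lie between 0.5 and 2.0 z and is shown as a range.

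**1. The plan's own sample size.** With the normal approximation, n = 2 × ((1.960 + 0.842) / 0.67)² = 34.97, so 35 per group. The t-based calculation gives 35.96, so 36, as stated; t-based power with 36 per group is 80.1%. Allowing for loss, 36 / 0.90 = 40. The stated figures reproduce, and power is computed on the 36 per group who remain.

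**2. Is the rule triggered at the planned loss?** 4/40 = 8/80 = 10.0%, which is not greater than 10%, so it is not. The ninth missing patient (9/80 = 11.25%) would trigger it.

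**3. How likely is it to stay off?** Treating losses as binomial with 80 patients, the probability of 8 or fewer missing is:

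| True loss probability | No imputation |
|---|---|
| 5% | about 98% |
| 10% | about 59% |
| 15% | about 13% |

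**4. Bias of a completers-only comparison.** In one group the full mean is (1 − f) × observed mean + f × missing mean, where f is the fraction missing. The observed mean therefore exceeds the full mean by f × D. The between-group difference shifts by f₁D₁ − f₂D₂. All three scenarios below have 8 of 80 missing, so a rule applied to the pooled variable is not triggered in any of them:

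| Missing by group | Deficit | Shift | Share of 0.67 |
|---|---|---|---|
| 6/40 vs 2/40 (15% vs 5%) | same D in both groups, 0.5 to 2.0 | 0.10 × D = 0.05 to 0.20 z | 7% to 30% |
| 4/40 vs 4/40 | D of 0.5 to 2.0 in one group, 0 in the other | 0.10 × D = 0.05 to 0.20 z | 7% to 30% |
| 4/40 vs 4/40 | same D in both groups | 0 | 0% |

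**The case against.** The strongest reply is that the defect is narrow and conditional. Ten per cent is a planning figure, and one more loss switches imputation on. The 10% is described as general loss to follow-up and is not attributed to death or stroke. Balanced losses with equal deficits give no bias. Exclusion criterion 6 (Subject selection) already removes patients whose comorbidities threaten a complete year of follow-up. Stroke and mortality are recorded separately, so an excess in one group would be visible. Handling of death and sensitivity analyses commonly belong in the analysis plan. All of this limits the size of the point. None of it justifies a trigger that ignores cause and balance and sits at the expected loss. The term complete-case is also an inference: the article does not use it, but it names no other method and powers the study on those who remain.

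A reader might infer more than the document supports:

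- **That patients with a stroke are dropped.** They are not. Both follow-up sections keep them, and only those who die, withdraw or cannot be tested are missing. The Discussion remark about untestable patients concerns a possible future use of neuroimaging. It shows that the problem is recognised, and does not describe this study's missing data.
- **That GCII itself could be removed above 10%.** Retention is decided by importance, and GCII is the named primary outcome, so the rule leads to imputation there.
- **That EuroScore II of 3-10% predicts how many of the four allowed losses per group will be deaths.** The article uses it only as a risk category.
- **That follow-up MRI is lost in the same way because of "cardiac rhythm complications (endo-cavitary pacemaker implant").** The article lists this as a complication and does not say that it prevents a scan.
- **That power falls because of the rule at, say, 20% loss.** At that loss the rule would call for imputation, so this is a separate question of attrition.

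**Conclusion.** The point holds in a limited form and is worth acting on. At the planned loss the imputation rule is not triggered, and the primary GCII comparison by default uses completers only. If missingness is informative and differs by procedure, a plausible shift is 0.05 to 0.20 z, or 7 to 30% of the planned 0.67, in favour of the procedure that loses more of its worst scores.

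This rests on three assumptions: a deficit of 0.5 to 2.0 z in the unseen scores, which the document does not give; a 15% versus 5% split, or a deficit confined to one group; and application of the threshold to the variable over both groups together, since the article sets no condition by group. It is a risk and not a certainty. The sample size is unaffected.

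**What to change.** Remove the 10% trigger for the GCII endpoint and name one primary method that applies at any level of missingness. Either of these would serve:

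- a longitudinal model of baseline, 1-month and 1-year GCII that keeps every patient with any score; or
- multiple imputation using information already collected: stroke, NIHSS, mRS and earlier GCII values. MMSE and MoCA add less, because they are given with the battery and will often be missing for the same patients.

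Neither settles the problem of death, because GCII after death is undefined. Add a sensitivity analysis that gives death or neurological inability to be tested the worst rank, and report missing GCII by group and cause.

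The cost is a change of wording and modest programming, with no new data collection and no change in sample size. The worst-rank analysis answers a slightly different question from the mean difference in GCII, so it belongs among the sensitivity analyses and should not replace the primary one.
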